### Prior experience with proposed combinations

The combination of chloroquine plus azithromycin is being studied in multiple settings under an active IND held by Pfizer Inc.  Clinical trials of this combination have been performed in India vs P.falciparum (21) and other such trials are currently in progress ([name], personal communication).  No safety concerns have been identified to date when these drugs are used in combination, and there does not appear to be any adverse pharmacokinetic interactions (52).

The combination of chloroquine and atovaquone/proguanil has not been previously studied in vivo (Glaxo Smith Kline, personal communication).

The combination of chloroquine and artesunate was studied in a double-blind, randomized, placebo-controlled trial in Sao Tome and Principe by Gill et al in 400 children with acute uncomplicated P.falciparum (53). The combined treatment was well tolerated, no serious drug-related adverse events were observed, and the addition of AS to CQ considerably improved treatment efficacy.  Multiple clinical trials using the combination of artesunate plus a related 4-aminoquinoline, amodiaquine, have not demonstrated any adverse pharmacokinetic or pharmacodynamic interactions.  The safety profile of this combination appears to be no different than the safety of the two individual components in this regimen.

## Potential Risks and Benefits

### Known potential risks

A complete listing of all adverse drug reactions associated with the study drugs is attached in Appendix II. Finger pricks and venipuncture are associated with small risks of bleeding, hematoma and infection. To minimize this risk, the skin is cleaned with alcohol prior to puncture, sterile, unused needles and lancets will always be used and pressure will be held at the puncture site after removal of the needle or lancet. Although the quantity of blood drawn would not lead to any ill effects on the participants’ health, some adults and rarely children feel faint with phlebotomy. The risks will be minimized by having trained technicians perform the procedure. Clinicians will be available for evaluation if there is any untoward effect.

### Known Potential Benefits

The participants in this study will have access to expeditious and high quality medical care for diagnosis and treatment of malaria, as well as other illnesses. They will also be treated with an effective antimalarial therapy. The anti-malaria treatment policy in Malawi is currently undergoing revision due to the poor efficacy of SP. As of the time of the writing of this protocol, a new treatment regimen has not been announced so the earliest implementation of a new policy is unlikely to occur until late 2007. All participants in this study will receive chloroquine, which we have shown to be safe and highly efficacious in this population, either alone or in combination with another active antimalarial medication.

# Objectives

## Study Objectives

The primary objective of this study is to compare the annual incidence of malaria.

Secondary objectives are:

1. Assess the antimalarial drug efficacy at first administration, by treatment arm.
2. Assess the antimalarial drug efficacy during subsequent episodes of malaria, by treatment arm.
3. Measure the prevalence of chloroquine resistant parasites during the trial, by treatment arm.
4. Assess the effect of each treatment arm on anemia at the end of study participation.
5. Assess the safety of repeated use of the drugs in each of the study arms.
6. Determine the chloroquine blood levels at which chloroquine sensitive and resistant parasites are able to cause infection.
7. Assess the effect of population movements on the risk of malaria infection
8. Assess the spatial patterns and the environmental determinants of malaria infection

## Study Outcome Measures

### Primary Outcome Measures

- The number of clinical malaria episodes per year of follow-up.

### Secondary Outcome Measures

1. To assess the antimalarial drug efficacy at first administration, by treatment arm.

- Rate of adequate clinical and parasitologic response 28 days after initial malaria

The 28 day outcomes represent the standard assessment of antimalarial efficacy and provide important information about the short term benefits of the drug. Since we will assess the ability of combination therapy to protect against the emergence of resistance, we are most interested in clinically apparent, in vivo drug efficacy.

- The incidence of new infections and recrudescent infections after initial treatment in each treatment arm

Parasites that emerge after treatment may be classified as new infections (arising from a new exposure) or recrudescent infections (arising from the original infection). Drugs that have poor efficacy but long half-lives may protect against new infections, but fail to cure the original infection completely. In contrast, shorter acting but highly effective medications may treat the initial infection successfully, but leave the individual susceptible to new infections in areas of high transmission. Distinguishing these two mechanisms will help to elucidate the complex interaction between the drugs and the parasite population.

1. To assess the antimalarial drug efficacy during subsequent episodes of malaria, by treatment arm.

- Rate of adequate clinical and parasitologic response 28 days after subsequent new episodes of malaria
- The incidence of new infections and recrudescent infections after subsequent new episodes of malaria

The same outcomes measured after the first administration will be monitored for subsequent administrations. This ability to detect efficacy after repeated use is a strength of the longitudinal study design.

- Incidence of severe malaria

Although children who present with severe malaria will be excluded from enrollment in the study, subsequent episodes of severe disease in study participants will be assessed as study endpoints. We would expect severe malaria to be rare in this population when children are treated promptly and effectively. A significant difference in the rate of severe disease, if detected, would be an important finding.

1. To measure the prevalence of chloroquine resistant parasites during the trial, by treatment arm.

- The prevalence of parasites with the mutation *pfcrt* 76T on Day 0 of each episode of malaria
- The prevalence of parasites with the mutation *pfcrt* 76T in cases of recurrent parasitemia after therapy

Because the genetic marker for CQ resistance is well-defined, we have the unique opportunity to assess not just resistance that is manifest on the clinical level, which may be confounded by acquired immunity, but also on the molecular level.

1. To assess the effect of each treatment arm on anemia at the end of study participation.

- Hemoglobin level without parasitemia at the close of the study

Childhood anemia is multifactorial in impoverished regions in sub-Saharan Africa and leads directly and indirectly to increased morbidity and mortality. Malaria is an important contributor to this pervasive problem (54). In our effort to simulate the public health implications of various antimalarial drug policies, we will attempt to assess the effect of each treatment arm on the general well-being of the children by measuring rates of anemia at the close of the study. We will not use the hemoglobin level at the start of the study as a point of comparison because all children will be enrolled with an episode of malaria, which will often be an acute cause of anemia. We will compare the prevalence of anemia, defined as hemoglobin <8 g/dL, at the end of one year of follow-up among all four arms.

1. To assess the safety of repeated use of the drugs in each of the study arms.

- Renal and hepatic function
- Neurological examination

Some of these medications have been associated with mild, transient abnormalities in hepatic and renal laboratory tests. We will assess these side effects in the context of repeated dosing over the course of the year. In addition, we will monitor the neurologic function of the participants due to the unique concerns associated with artemisinin derivatives.

1. To determine the chloroquine blood levels at which chloroquine sensitive and resistant parasites are able to cause infection.

- Chloroquine pharmacokinetic curve for the population
- Drug concentration at the time of parasitemia

Ideally, we would like to know the drug level just prior to a detectable parasitemia in the participant since at that level, parasites were able to begin to replicate. Since it is impossible to anticipate when a new patent parasitemia will occur, we will attempt to predict the level retrospectively by obtaining the pharmacokinetic curve in the population. We will also measure the level at the time of recurrent parasitemia in case the participant was found to vary significantly from the mean.

1. Assess the effect of population movements on the risk of malaria infection.

- Risk of malaria in children who traveled outside the city compared to those who did not.

Our interest is the first incident of malaria. Malaria illness will be defined as any level of microscopy-confirmed *Plasmodium falciparum* parasitemia accompanied by signs or symptoms consistent with malaria either leading to treatment-seeking behavior or reported during follow-up visits. This definition is more inclusive since practicing physicians in a malaria endemic area would treat a person who presents complaining of illness and who had documented parasitemia. This definition will enable the longitudinal study to capture all first episodes of malaria illness that would be treated under standard medical practice. Time to malaria illness after baseline is defined as number ofdays without malaria illness after baseline up to the date of the first illness. Dates will be recordedfor all the events occurring prior to or during follow-up.

1. Assess the spatial patterns and the environmental determinants of malaria infection

- Distribution of malaria cases in relation to environmental factors in Ndirande.

In order to evaluate whether there is clustering of cases and/or spatial correlation with environmental variables, we will carefully analyze the spatio-temporal pattern of all cases. All new malaria illnesses after the initial treatment will be escorted home and their location geo-referenced using GPS. Information will be entered into ArcGIS (*ESRI, Redland, CA*) to create a spatial point pattern. This will be linked to the database with information on health, demographic, economic, social, ecological and agricultural characteristics.

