## Sample Size Considerations

In a previous longitudinal study of malaria in this population, we found that the mean annual incidence of malaria was approximately 2.5 episodes per year (59) with a standard deviation of approximately 2. Chloroquine is presently highly effective in treating malaria and has a prolonged prophylactic effect, so we have estimated a mean rate of 1.5 malaria episodes per year with chloroquine alone. We derived the sample size required to detect a decrease in the mean to 1.0 episodes per year assuming a Poisson distribution and using a 2 sided test with alpha= .05/3=.0166. The test size was adjusted to accommodate the 3 treatment versus control comparisons. With the above requirements and for a 2 treatment contrast, 120 subjects with complete observation are required per treatment arm to have 90% power (PASS 2005). To account for migration and other causes of attrition, we will enroll an additional 33% (40 subjects) in each regimen. We will accrue 160 per arm for a total of 640 subjects.

Because of the currently estimated efficacy of chloroquine alone in Malawi (in excess of 95%), we are unlikely to determine differences in initial administration (day 28) efficacy between the treatment arms. Power is limited as all arms should have very few early failures. Rates of anemia (<8 mg/dl) at the end of one year should be available in ~120 subjects per arm. The 95% CI half-width for the difference in anemia rates, calculating the variance with a rate of .2, is approximately .10. Thus, the selected sample size should be informative about larger treatment arm differences in anemia rates.

To determine the population pharmacokinetic curve for chloroquine, we have designed a randomized unbalanced study. All participants will have chloroquine levels determined prior to drug administration, at day 14 and at one additional randomly assigned time point. The assignment will be weighted to increase measurement on day two. Planned Interim Analyses

The DSMB will decide when it would like to conduct the interim analysis. The data to be reviewed at this meeting will include safety and efficacy data.

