## Final Analysis Plan

The final analysis of the primary objective will be a comparison of incidence rates of malaria treatment episodes per year of follow-up (not including the first infection occurring at enrollment) in each arm of the study. The rates and 95% confidence intervals will be calculated using Poisson distribution. Reported antimalarial drug use without documented positive malaria smear will not count as a malaria treatment episode. Malaria episodes treated with non-study medicines at Queen Elizabeth Central Hospital with verified positive malaria smears will be counted as malaria treatment episodes, and any such treatments will be compared among groups to rule out bias due to different rates of non-study treatment. Withdrawal of participation is described above and includes participants who miss ≥ 2 consecutive routine follow-up visits. For the primary study endpoint, follow-up time for participants while they are enrolled in the study will be included in the analysis. For participants who were withdrawn after missing > 2 consecutive follow-up visits, time after the last visit will be censored from incidence analysis.

Drug efficacy for the first and subsequent episodes of malaria will be compared using Kaplan-Meier 28-day survival estimated and compared using Cox proportional hazards regression. Per-protocol analysis will be used to compare treatment efficacy, with data excluded from treatment episodes for which treatment outcome cannot be determined. Survival analysis will also be used to assess time to first resistant infection in each arm. Categorical data including episodes of liver, kidney or neurological toxicity and presence of anemia will be compared using 2 analysis. Logistic regression will be used to adjust for covariates.

Survival analysis will be used to assess the role of travel outside of Blantyre and bed net use on the risk for malarial and time to first malaria episode. This analysis will be conducted both with and without the inclusion of treatment arm as a covariate in the analysis.

Data will be entered in to the database on the computers at the field site. On a daily basis, the data will be transferred via the internet to the EMMES corporation web-based system.

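### The anemia outcome is defined on parasite-free hemoglobin in one place and on all completers elsewhere; if the restriction is applied, it conditions the comparison on a post-randomisation state

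*Protocol*

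**What the plan says.** Protocol 3.2.2 (Secondary Outcome Measures) lists one outcome measure for the anemia objective: "Hemoglobin level without parasitemia at the close of the study". The explanatory text below it describes a different quantity: "We will compare the prevalence of anemia, defined as hemoglobin <8 g/dL, at the end of one year of follow-up among all four arms". That sentence does not repeat the restriction to children without parasites.

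The same text sets the enrolment value aside: "We will not use the hemoglobin level at the start of the study as a point of comparison". The reason given is that every child enters the trial while ill with malaria, and that illness can itself lower hemoglobin for a time.

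Section 11.2 (Sample Size Considerations) plans precision on the completers: "Rates of anemia (<8 mg/dl) at the end of one year should be available in ~120 subjects per arm". On the precision that this gives, it says: "The 95% CI half-width for the difference in anemia rates, calculating the variance with a rate of .2, is approximately .10". The difference between 160 enrolled and 120 analysed is explained by loss to follow-up only: "To account for migration and other causes of attrition, we will enroll an additional 33% (40 subjects) in each regimen".

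Section 11.3 (Final Analysis Plan) treats the outcome as categorical: "Categorical data including episodes of liver, kidney or neurological toxicity and presence of anemia will be compared using" a chi-square analysis, with logistic regression to adjust for covariates that are not named.

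**The concern.** Two definitions of one endpoint are in force. The outcome line is a level in parasite-free children. The comparison sentence and 11.2 describe a proportion in all completers. The two can give different answers, and the choice could be made after the data are seen.

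The restriction matters more than the wording suggests. Parasitemia at study close can depend on the assigned drug; the trial's primary outcome is the number of malaria episodes by arm. Keeping only smear-negative children compares subsets that are no longer the randomised groups. It also removes any effect on hemoglobin that runs through infection present at the end, although the stated aim is to reflect what each drug policy would do to children's health overall.

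**Working it through.** **1. The plan's own precision figure.** Inputs from 11.2: n = 120 per arm, rate 0.2, 95% interval. The half-width is 1.96 × √(2 × 0.2 × 0.8 / n).

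- n = 120: 1.96 × √(0.32/120) = 0.101, which matches the stated figure of about .10. So 11.2 counts every completer.

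**2. The same figure if smear-positive children are dropped.** The protocol gives no end-of-study parasitemia rate, so 10% and 20% are assumptions. The anemia rate is held at 0.2.

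- 10% dropped, n = 108: 1.96 × √(0.32/108) = 0.107
- 20% dropped, n = 96: 1.96 × √(0.32/96) = 0.113

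**3. What the restriction can hide.** All inputs here are assumed. Let 20% of one arm and 10% of another be parasitemic at the end, with anemia in 40% of parasitemic and 15% of parasite-free children in both arms.

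- All children: 0.20 × 0.40 + 0.80 × 0.15 = 0.200, against 0.10 × 0.40 + 0.90 × 0.15 = 0.175. The difference is 2.5 points.
- Parasite-free children only: 0.15 against 0.15. The difference is 0.
- With 30% against 10% parasitemic: 0.225 − 0.175 = 5 points among all children, and still 0 in the subset.

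**4. Whether the visit rules remove the problem.** Under Final Study Visit, a child still in efficacy follow-up has the last visit moved to day 28 or to the point where the efficacy endpoint is reached. Section 4.3 requires parasitemia for both late clinical and late parasitologic failure. A child whose last treatment ends in such a failure can therefore have the closing hemoglobin taken while parasitemic. Under Follow-up, smears at routine visits are read at once only when illness is reported or malaria is suspected, so symptom-free positives at visit 13 come to light later. Deferral lowers the number of smear-positive final visits but does not bring it to zero.

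**5. What the cut at 8 g/dL costs.** For a normal variable cut at its p-quantile, the information kept under a location shift is φ(z_p)² / [p(1 − p)]. The protocol gives no hemoglobin distribution, so normality is assumed.

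- p = 0.20 (the planning rate): 0.280² / 0.16 = 0.49. About 51% is lost, and 120 children act like about 59.
- p = 0.50: 36% lost. p = 0.05: 78% lost.

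For a fall from 20% to 10% with 120 per arm (a shift of 0.44 SD, two-sided 0.05), power is 58% for the proportion and 93% for the mean.

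**6. Day-0 hemoglobin.** The value exists: hemoglobin is measured at screening and a blood count is taken at enrolment. In a linear model, adjustment multiplies the variance by 1 − ρ². At ρ = 0.3 that is 0.91, and at ρ = 0.5 it is 0.75. Both correlations are assumptions.

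**The case against.** The restriction stands in one line only; the comparison sentence, 11.2 and 11.3 do not carry it. A reader might infer that the protocol orders smear-positive children to be excluded, and that this removes more children from the worse arm. The documents support neither: no text states an exclusion and none fixes a direction. What stands is that the definitions conflict, and that the outcome line, if followed, conditions on a post-randomisation state.

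There is also a visible reason for reading hemoglobin away from acute infection. Section 3.2.2 calls malaria an acute cause of anemia, and 4.3 notes that hemoglobin often falls even under effective therapy. That makes the parasite-free value a reasonable supplementary quantity. It does not make the selected comparison a randomised one.

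A reader might also infer that the plan throws away half its information. That figure belongs to the 8 g/dL cut alone, at a 20% rate and under normality. The prevalence is a deliberate public-health measure that a mean difference does not replace. The outcome line itself names a level, so a statistical analysis plan could analyse hemoglobin continuously as well.

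Lastly, the enrolment value is declined only as a point of comparison, which is sound against change from baseline, and 11.3 leaves covariates open. Not naming it as a covariate is therefore no error. The stated reason simply gives no ground for leaving it out of the model.

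**Conclusion.** The point holds as an inconsistency with a real consequence. The outcome line and the planned comparison describe different quantities in different children, and a statistical analysis plan cannot satisfy both. If the outcome line is applied, the randomised comparison is lost for this endpoint and an effect through current infection can disappear: 2.5 to 5 points in the illustration, whose inputs are all assumed. The loss of precision from dropping children is modest, .101 to .107–.113 at 10–20% smear-positive, also assumed.

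The cut and the unused day-0 value are opportunities to gain precision, not faults in the plan. Their size depends on the anemia rate, on normality and on a correlation that the protocol does not give. The mg/dl in 11.2 is a plain unit error, since 3.2.2 gives g/dL. The endpoint is secondary and the primary analysis is not touched.

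**What to change.** - In 3.2.2, define the endpoint as hemoglobin at the final study visit (visit 13, or the deferred visit under section 7.4, Final Study Visit) in all randomised children with a value, whatever the smear result. Make the parasite-free subset a sensitivity analysis.
- Keep the prevalence below 8 g/dL as the main comparison. Name day-0 hemoglobin and age as covariates in the logistic regression already planned in 11.3.
- Report mean hemoglobin by arm beside it, from a linear model with the same covariates.
- Correct the unit in 11.2 to g/dL.

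This needs wording and analysis only. Hemoglobin, blood count and smear are already collected at the visits concerned. The downside is that the main estimate will include the acute effect of infection present at the last visit; the sensitivity analysis shows how much of the result that accounts for.

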## Follow-up

Follow-up visits may be one of four types: day of new malaria episode diagnosis, drug efficacy follow-up, routine visit, unscheduled visit.

On the initial day of a new diagnosis, a venipuncture will be performed to obtain the following studies: filter paper sample for molecular analysis, CBC, ALT, creatinine, chloroquine level and specimen for cryopreservation of parasites. The total volume will be approximately 3.5-5 mL.

Drug efficacy follow-up occurs after the initial and all subsequent administrations of the study drug to treat symptomatic malaria. Visits will occur on days 1, 2, 3, 7, 14, 21, 28. Hemoglobin, malaria smears and filter papers will be obtained on each of those days and a physical examination will be completed. Specimens from a finger prick will be obtained on two occasions after day 0: on day 14 and an additional day assigned randomly at enrollment. Chloroquine level, CBC, ALT and creatinine will be measured routinely on day 14, after acute changes associated with malaria should have resolved If the participant misses the visit corresponding to the day a chloroquine level and/or CBC, ALT and creatinine arescheduled to be collected, the study team will endeavor to collect this specimen as the next visit. Drug administration will occur on days 1 (2nd dose) and 2 (3rd dose).If treatment failure occurs after day 3 and the parasite density is >10,000/mm3, blood will be collected to measure the chloroquine level and for cryopreservation of malaria parasites for further in vitro susceptibility testing. A neurologic exam will occur on day 28.

Routine visits occur every four weeks. Malaria smear and filter paper will be obtained. The malaria smear will be read at that time only if there are complaints of an illness or the clinician suspects malaria. The encounter will include an interval history, questions about off-study drug use, recent travel, bed net use and a physical examination. At routine visits 4, 8 and 13, CBC, ALT and creatinine will be obtained for safety monitoring surveillance. All blood specimens will be collected from a finger prick except for the specimens for cryopreservation which require 3-5 ml. On all other days, the amount of blood drawn from the finger prick will range from 0.05 ml (malaria smear, hemoglobin, filter paper) to approximately 0.5 ml (malaria smear, hemoglobin, filter paper, CBC, ALT, creatinine and chloroquine level).

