## Clinical Evaluations

*History-comprehensive*

- The medications administered to the child in the past week
- Any underlying medical conditions
- Allergies
- Recent travel history and bed net use

*History-possible adverse drug reactions and interval*

A standardized checklist in the case report form includes symptoms of malaria, as well as most common adverse effects of the drugs being administered.

*Questioning about antimalarial use*

The parent/guardian will be asked if any drugs have been administered to the child in the interval since the last visit. The clinician will then specifically ask about the commonly administered antimalarial drugs.

*Physical examination*

The physical examination includes vital signs (temperature, heart rate, respiratory rate), weight, height and a complete physical examination that focuses on: signs of malaria, signs of non-malaria sources of fever and adverse reactions to the medications.

*Neurological examination*

A basic age-appropriate neurological examination will be conducted at the end of every episode of malaria treatment if the participant is not ill (day 28) and also at visit number 4, 8 and 13. See appendix IV.

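### Secondary objective 7 compares children by whether they travelled, although travel accrues after time zero: read literally, this makes travel look protective or dilutes a real effect, depending on which trips count

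*Protocol*

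**What the plan says.** Protocol section 3.2.2 (Secondary Outcome Measures) defines the population-movement measure as "Risk of malaria in children who traveled outside the city compared to those who did not". It then fixes the event ("Our interest is the first incident of malaria") and the clock, which counts malaria-free days from baseline to that illness.

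Section 11.3 (Final Analysis Plan) gives the method: "Survival analysis will be used to assess the role of travel outside of Blantyre and bed net use on the risk for malarial", and on time to the first episode. On covariates it adds "This analysis will be conducted both with and without the inclusion of treatment arm as a covariate in the analysis".

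Travel is ascertained repeatedly. Section 7.3 (Follow-up) says of the routine four-weekly visit: "The encounter will include an interval history, questions about off-study drug use, recent travel, bed net use and a physical examination". Section 8.1 (Clinical Evaluations) also lists "Recent travel history and bed net use" under the comprehensive history, which the schedule in Appendix I places on day 0 as well as at routine visits.

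The protocol does not say which trips make a child a traveller, how long a trip counts as exposure, or whether a child can change group during follow-up.

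**The concern.** Travel during follow-up is not known at time zero. Sorting children into two groups by it, with time counted from baseline, can be done in two natural ways.

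- **Trips up to the first malaria.** A child joins the travelled group only by staying malaria-free until the trip. Those malaria-free days are then counted as travellers' time, and children who fall ill early go mostly to the other group. This is immortal time bias.
- **Trips at any time in the year.** Trips after the illness also classify the child, and time before a trip counts as exposed. This is exposure misclassification, and it pulls a real effect towards 1.

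The objective asks whether movement out of the city changes malaria risk. Under the first coding the answer could be reported with the wrong sign; under the second a short-lived effect could be nearly lost.

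**Working it through.** The protocol gives no effect size, power or trip rate for this comparison, so there is no stated figure to reproduce.

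**Inputs**

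- Malaria rate λ: 1.5 and 1.0 per year, the two design rates in section 11.2, used here as the hazard of first illness.
- Follow-up: one year per child; 640 children.
- Assumed, not in the documents: first trips at rate μ = 0.5, 1 or 2 per year, independent of malaria; a true hazard ratio of 1 or 2; raised risk for 28 days after a trip, or lasting.

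**1. No true effect, travel counted up to the first malaria (exact).** Let a = λ + μ. Per child:

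- Total events = 1 − e^(−λ); total time = (1 − e^(−λ))/λ.
- Events in non-travellers = (λ/a)(1 − e^(−a)).
- Time in non-travellers = (λ/a²)[1 − e^(−a)(1 + a)] + e^(−a).
- Travellers have the remainder.

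With λ = 1.5, μ = 1, a = 2.5 and e^(−2.5) = 0.0821:

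- Non-travellers: events 0.6 × 0.9179 = 0.5507; time 0.24 × 0.7127 + 0.0821 = 0.2531; rate 2.18 per year.
- Travellers: events 0.7769 − 0.5507 = 0.2261; time 0.5179 − 0.2531 = 0.2648; rate 0.85 per year.
- Rate ratio = 0.85/2.18 = **0.39**, although the true value is 1.

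The misplaced time can be isolated. Travellers' time after the trip is 0.2261/1.5 = 0.1507, so 0.2648 − 0.1507 = 0.1140 came before it. Moving that to the unexposed side gives 0.5507/(0.2531 + 0.1140) = 1.50 per year, and after the trip 0.2261/0.1507 = 1.50. The ratio returns to 1.00.

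A simple one-year risk comparison does not escape. The travelled group is (μ/a)(1 − e^(−a)) = 0.3672 of children, so the risks are 0.2261/0.3672 = 0.616 and 0.5507/0.6328 = 0.870, a ratio of 0.71.

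**2. Range.** For λ from 1.0 to 1.5 and μ from 0.5 to 2, the same formulas give 0.28 to 0.44. Every child has just been treated with chloroquine, so a constant hazard from day 0 is too simple. If no malaria can occur in an assumed first 28 or 56 days, simulation at λ = 1.5 and μ = 1 gives 0.47 or 0.53. Over all rates the ranges are 0.35–0.52 and 0.40–0.58. Together: roughly 0.3 to 0.6.

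**3. All codings compared.** Cox models on 640 simulated children over one year, 20 to 25 replicates per scenario, no protected period. Entries are the lowest and highest mean hazard ratio over both malaria rates and all three trip rates.

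| Coding of travel | No effect | Doubling for 28 days | Lasting doubling |
|---|---|---|---|
| Up to first malaria | 0.27–0.44 | 0.33–0.52 | 0.47–0.76 |
| Any time in the year | 0.98–1.02 | 1.06–1.16 | 1.38–1.54 |
| Time-varying | 0.96–1.06 | 1.94–2.05 | 1.95–2.13 |

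Of these codings, only the time-varying one recovers the truth in every column.

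**The case against.** The strongest reply is that the protocol names no grouping rule. Survival analysis covers a time-varying Cox model as well as a fixed one, exposure coding is usually left to the statistical analysis plan, and travel is collected at every routine visit, which is what a time-varying analysis needs. Much of this stands: the data are adequate, and an analysis plan that is not shown may resolve the matter. It does not remove the point, because the protocol itself fixes the contrast between children, the event and the time origin. An analysis plan that implements those words as a grouping inherits the problem.

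A reader might infer that the stated comparison necessarily builds in immortal time and reverses the sign. The documents do not support that. Reversal needs travel to be counted only up to the first malaria. Counting it over the whole year leaves the null unbiased and keeps the right sign, with dilution only. Using travel before baseline, which the day 0 history would supply, creates no immortal time at all. However, no section names earlier travel as the exposure, and the repeated follow-up questions suggest otherwise.

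It is also fair that the sizes depend on assumptions. The drug-protected period weakens the spurious protection from 0.39 to about 0.5 in the central case but does not remove it. No bias has been estimated for bed net use.

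**Conclusion.** The point holds as a badly fixed comparison in a secondary, non-randomised objective. Read as a grouping of children by travel during follow-up, it gives either spurious protection (rate ratio roughly 0.3 to 0.6 with no true effect) or dilution (a 28-day doubling seen as about 1.1, a lasting one as about 1.4 to 1.5). Which of the two occurs depends on a coding choice that the protocol leaves open. The sizes rest on 0.5 to 2 trips per year, malaria rates of 1.0 to 1.5 per year, trips independent of malaria, and the assumed effects and protected periods. The directions were the same in every scenario examined.

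The primary treatment comparison, the sample size and the safety assessments are not affected. The wording should be amended before analysis, but this does not threaten the trial's main conclusion.

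**What to change.** In sections 3.2.2 and 11.3, state that travel during follow-up enters the Cox model as a time-varying covariate: a child is exposed from each trip for a pre-stated window, unexposed otherwise, and updated at each visit. Fit it in counting-process form, with and without treatment arm as already planned. Code bed net use as time-updated in the same model, since it is asked at the same visits and named in the same sentence of section 11.3.

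The cost is analysis wording and a little data preparation; no extra visits, samples or children are needed. The one limit is precision: unless trip dates are recorded, the timing of a trip is known only to about the four-week interval between visits, and the exposure window should be chosen with that in mind.
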